### Sample size considerations

The overall study sample size has been calculated to determine the structural validity of the instrument using Rasch analysis. Our Rasch model assumes that item calibrations are within ±½ logit from stable values, with a 99% confidence interval. This gives an overall sample size of between 108 and 243, best to poor targeting [64]. We expect 200 participants will complete the study, from a sample of 250 participants. This is in keeping with COSMIN recommendations for Rasch analysis [56–58].

For longitudinal analysis over 12 weeks, we predict that *n* = 200 people will complete both study visits. The power calculation for a linear multiple regression with CAP-RA plus 5 baseline covariates (each assumed to have a correlation coefficient of 0.15 with the 12-week pain) yielded a sample size of *n* = 164 for α = 0.05 and power = 0.95.

Seventy-seven participants are required for the reliability study to estimate an ICC of 0.8, with 2 ratings, alpha of 0.05, 80% power, and a lower limit ICC not less than 0.6. Sample size calculation was implemented in R using “ICC.sample.size package” [65, 66].

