### Statistical analysis

The primary objective of the study is to determine the psychometric properties of the new CAP-RA questionnaire. The psychometric properties examined will include structural validity, construct hypothesis testing, internal consistency, reliability, measurement error and criterion validity, in accordance with Consensus-based Standards for the selection of health Measurement Instruments (COSMIN) guidelines [56–58].

Structural validity measures the degree to which the scores in a patient reported outcome measure reflect the dimensionality of the construct to be measured. Structural validity will be assessed using confirmatory factor analysis (CFA) and Rasch modelling. A suitable polytomous Rasch model will be selected [56]. The unidimensional and local independence assumptions will be examined and model fit parameters will be estimated [59]. The construct validity of the CAP-RA questionnaire, a measure of the degree to which scores are consistent with a hypothesis that is based on the assumption that the PROM validly measures the intended construct, will be investigated using confirmatory factor analysis. Appropriate fit statistics will be calculated [60]. Internal consistency, which is a measure of the degree of interrelatedness among items in the questionnaire will be estimated using Cronbach’s alpha, with a value greater than 0.70 signifying acceptable internal consistency [61].

Test-retest reliability will be estimated using the Intraclass Correlation Coefficient, with acceptable values ≥0.70 [62]. Measurement error will be estimated by the Standard Error of Measurement (SEM), Smallest Detectable Change (SDC) and the Limits of Agreement (LoA). Criterion validity will be a measure of the degree to which the instrument is an adequate reflection of central sensitisation.

The relationship between baseline CAP-RA scores and pain outcomes will be measured using regression analysis, with 12-week pain as the outcome variable and baseline characteristics as covariates.

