Secondary objectives will be addressed using appropriate regression analysis. For example, the association between fatigue and central sensitization will be examined using linear or non-linear regression analysis, based on the distribution of the data, and the course of fatigue will be examined using linear or non-linear mixed effect models as indicated. CAP-RA questionnaire thresholds for delimiting high levels of central pain mechanisms will be derived through receiver operating curves plotted using dichotomised outcome measures, such as the different QST measurements [56, 63].

Analyses will be undertaken using appropriate statistical software. *P* values less than or equal to 0.05 will be considered statistically significant unless otherwise stated.

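### The 0.95 power at n = 164 fits a joint test of all predictors; CAP-RA's own coefficient, the stated target, has about 62% power at 200 completers

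*Protocol article*

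**What the plan says.** Under Sample size considerations, the protocol article first sizes the whole study on the Rasch analysis, with 250 enrolled and 200 expected to finish. It then treats the longitudinal analysis separately. It expects 200 at both visits ("we predict that *n* = 200 people will complete both study visits") and gives the calculation: "The power calculation for a linear multiple regression with CAP-RA plus 5 baseline covariates (each assumed to have a correlation coefficient of 0.15" with 12-week pain), which "yielded a sample size of *n* = 164 for α = 0.05 and power = 0.95".

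Under Statistical analysis, the regression has a specific target: "The relationship between baseline CAP-RA scores and pain outcomes will be measured using regression analysis, with 12-week pain as the outcome variable", with baseline characteristics as covariates. The general significance rule there is that "values less than or equal to 0.05 will be considered statistically significant unless otherwise stated".

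Neither section says whether the 0.95 refers to the model as a whole or to the CAP-RA term. No correlation among the six predictors is given.

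**The concern.** Two different tests can be powered in this model. The joint test asks whether the predictors together explain any variation in 12-week pain. The coefficient test asks whether CAP-RA explains anything once the other five are in the model. The analysis section asks the second question. A figure of 95% at 164, with six effects as small as r = 0.15, looks attainable only for the first.

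The difference matters because the joint test says little about CAP-RA: the other covariates alone can make it significant. A reader who takes 0.95 as the chance of detecting CAP-RA's association would be too confident in the design, and could give a non-significant CAP-RA coefficient more weight than it deserves.

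**Working it through.** **Inputs from the article.** Six predictors (CAP-RA plus 5), r = 0.15 each with 12-week pain, α = 0.05, power 0.95, n = 164, 200 completers.

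**Assumption, not in the article.** Predictors are mutually uncorrelated unless stated otherwise.

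**Method.** Noncentral F with noncentrality λ = n × f². Numerator df is the number of terms tested; denominator df is n − p − 1 for p predictors.

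**Step 1. Where 164 comes from.** With uncorrelated predictors, R² = 6 × 0.15² = 0.135 and f² = 0.135/0.865 = 0.156.

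| Joint test | f² | n for power 0.95 | Power at 164 |
|---|---|---|---|
| Six predictors, uncorrelated | 0.156 | 141 | 0.978 |
| Six predictors, R² 0.135 used as f² | 0.135 | 161 | 0.954 |
| Five predictors, R² = 5 × 0.0225 = 0.1125, f² = 0.1125/0.8875 | 0.127 | 162 | 0.953 |
| Six predictors, pairwise correlation 0.03, R² = 0.135/1.15 = 0.117 | 0.133 | 164 | 0.951 |

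Several joint-test readings reach or nearly reach 164, and the article does not show which was used.

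**Step 2. Can a test of one coefficient give 164?** No, not with r = 0.15:

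- f² = 0.0225/0.865 = 0.0260: n = 502 for 95% power (418 one-sided).
- 0.15 taken as the partial correlation, f² = 0.0225/0.9775 = 0.0230: n = 567 (472 one-sided).

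**Step 3. Power for the CAP-RA coefficient (1 df, two-sided 0.05).**

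| Reading of r = 0.15 | n = 164 | n = 200 |
|---|---|---|
| Six uncorrelated predictors (λ = 4.27 and 5.20) | 53.7% | 62.2% |
| 0.15 is the partial correlation | 48.9% | 57.0% |

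On the first row, 80% power needs 304 completers.

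**Step 4. Positive correlation among predictors.** With a common correlation ρ, R² for k predictors is k × 0.0225/(1 + (k − 1)ρ). CAP-RA's f² is (R² with six − R² with five)/(1 − R² with six). The values of ρ are illustrative.

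| ρ | CAP-RA power at 164 | at 200 |
|---|---|---|
| 0.03 | 42% | 50% |
| 0.1 | 26% | 30% |
| 0.2 | 15% | 18% |
| 0.3 | 11% | 12% |

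The row ρ = 0.03 is the one that gives exactly 164 for the six-predictor joint test.

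**Step 5. Does the joint test depend on CAP-RA?** Set CAP-RA's contribution to zero and keep the other five at 0.15: R² = 0.1125, f² = 0.127, 6 df. The joint test is still significant with probability 94% at 164 and 98% at 200.

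**Step 6. If the 0.15 covers only the five covariates.** For a CAP-RA correlation r, f² = r²/(1 − 0.1125 − r²). At 164, power reaches 95% at r of about 0.257 (f² = 0.080). At 200, power is 86% for r = 0.20 and 97% for r = 0.25.

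**Step 7. What 200 completers support.** With f² = r²/(1 − r²) for a partial correlation r: 0.20 gives 82% and 0.25 gives 95%.

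**The case against.** The article never says that its 0.95 is for the CAP-RA coefficient, so it makes no explicit false claim. That the figure belongs to a joint test is an inference from which formulas land near 164. This stands, and it is why the remedy begins by asking for the hypothesis to be named. The inference is nonetheless firm, because no single-coefficient calculation with r = 0.15 comes near 164.

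The word introducing the 0.15 may refer only to the five covariates. That also stands. The 54% and 62% would then not follow, and CAP-RA could be well powered if its correlation were 0.20 to 0.25. But the one effect that the analysis targets would then be missing from its own power calculation.

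A reader might infer that 164 is an arithmetic error and should be 141. The documents do not support this. The 141 rests on zero correlation among predictors, which the article does not state, and a common correlation of only about 0.03 gives 164 exactly. Entering R² as f² is one possible route to a figure near 164, not an established one.

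A reader might also infer that the study is too small overall. It is not sized on this regression: enrolment follows from the Rasch analysis, the primary objective is psychometric, and pain-outcome prediction is listed among the secondary objectives. Finally, the article sets no rule for reading a null result, so a misreading is a risk and not something the plan prescribes.

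**Conclusion.** The point holds as a mismatch between a printed power figure and the inference it is offered to support. If 0.15 applies to all six predictors, 0.95 at n = 164 describes a joint test, while the targeted CAP-RA coefficient has about 54% power at 164 and 62% at 200 (49% and 57% if 0.15 is a partial correlation). At 200 completers, a true association of that size would be missed in roughly 4 studies of 10. The 62% assumes uncorrelated predictors; a shared positive correlation with equal r lowers it, but by an amount the article gives no basis to fix. If 0.15 applies only to the covariates, the CAP-RA effect is unstated. Either way, the calculation does not show 95% power for CAP-RA's predictive validity.

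This should be fixed, but it does not threaten the study: it concerns a secondary objective and does not drive enrolment.

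**What to change.** In the sample size section, either state that the 0.95 at n = 164 refers to the joint test of the predictors, or remove it as support for CAP-RA's predictive validity. Make clear which predictors the 0.15 describes. Then give power for the CAP-RA coefficient, or equivalently for its R² increment when added last. Suggested wording: with 200 completers, the test of the CAP-RA coefficient given five covariates has about 80% power for a partial correlation of 0.20 and 95% for 0.25; at 0.15, power is about 57–62%, the upper figure assuming uncorrelated predictors. Do not substitute n = 141.

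The cost is a few sentences and a less favourable stated figure. Enrolment, visits and data collection are unchanged.

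### The retest sample size of 77 does not follow from its stated inputs: a lower limit of 0.6 needs about 50 (two-sided) or 39 (one-sided)

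*Protocol article*

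**What the plan says.** The protocol article's Sample size considerations section justifies the retest substudy in one sentence: "Seventy-seven participants are required for the reliability study to estimate an ICC of 0.8, with 2 ratings, alpha of 0.05, 80% power". The same sentence closes with the bound to be met, "a lower limit ICC not less than 0.6". The section names an R package for the calculation. It does not say whether alpha is one- or two-sided, and it states no allowance for forms that are not returned.

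Under Study regimen and Additional data collection, the form is sent to 80 consecutive participants one week after baseline.

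The Statistical analysis section sets the benchmark: "Test-retest reliability will be estimated using the Intraclass Correlation Coefficient, with acceptable values ≥0.70". It lists reliability among the psychometric properties that make up the primary objective.

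**The concern.** The sentence gives every input needed to recompute the number except the sidedness of alpha. A reader who does so gets a clearly smaller figure under either choice, so the statement contradicts itself. Either the lower limit, the power or the number is not what was used.

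The sentence also tells readers what the substudy can establish. As written, it suggests that 77 retests are just enough to rule out an ICC of 0.6. In fact they do considerably better than that. The sentence is also silent on how 0.6 relates to the 0.70 benchmark, so a reader cannot tell whether the substudy is meant to show that reliability is at least 0.70 or only to estimate it. Because reliability belongs to the primary objective, the stated basis should be reproducible and its reach clear.

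**Working it through.** **Inputs** (all from Sample size considerations unless noted)

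- Expected ICC ρ1 = 0.8
- Lower limit, taken as the null value, ρ0 = 0.6
- Ratings k = 2
- Alpha 0.05, sidedness not stated, so both were tried
- Power 80%
- Stated result 77
- Benchmark 0.70 (Statistical analysis)

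**Step 1: the stated figure from the stated inputs**

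The Walter–Eliasziw–Donner formula is

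n = 1 + 2k(zα + zβ)² / [(k − 1)(ln C0)²], with C0 = [1 + kρ0/(1 − ρ0)] / [1 + kρ1/(1 − ρ1)].

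For ρ0 = 0.6, C0 = (1 + 3)/(1 + 8) = 4/9 and (ln C0)² = 0.6576.

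- Two-sided: (1.960 + 0.842)² = 7.849, so n = 1 + 4 × 7.849/0.6576 = 48.7, that is 49.
- One-sided: (1.645 + 0.842)² = 6.183, so n = 1 + 4 × 6.183/0.6576 = 38.6, that is 39.

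The exact check uses the one-way F test with n − 1 and n degrees of freedom. Power is P[F > Fcrit × R0/R1], where R = (1 + ρ)/(1 − ρ). The smallest n reaching 80% is 50 two-sided (power 80.7%) and 39 one-sided (80.1%).

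Other approximations do not recover 77 either. Fisher's z gives 50 to 51 two-sided and 40 to 41 one-sided. Wald-type variances give 27, 62 or 82 two-sided and 21, 47 or 65 one-sided. The stated figure is not reproduced.

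**Step 2: what 77 delivers against 0.6**

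By the approximation, zβ = |ln C0| × √[(n − 1)/4] − zα = 0.811 × √19 − 1.960 = 1.575, which is 94% power two-sided. The exact F test gives 94.1% two-sided and 97.0% one-sided.

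**Step 3: which lower limit gives 77**

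For ρ0 = 0.65, C0 = 4.714/9 = 0.5238 and (ln C0)² = 0.4181. Two-sided, n = 1 + 4 × 7.849/0.4181 = 76.1, that is 77. The exact F test also gives 77 (power 79.7% at 76 and 80.2% at 77). One-sided, 0.65 gives 61, and the limit that yields 77 is about 0.67.

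The match with 0.65 is exact but not unique. For example, two-sided alpha 0.025 with 90% power against 0.6 gives 76.5 by the approximation (78 exactly). The 39 from the one-sided calculation, inflated for about 50% non-return, also lands on 77. The article states neither.

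**Step 4: 77 against the 0.70 benchmark**

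| Quantity at n = 77 | Result |
|---|---|
| True ICC 0.8: chance that the estimate is at least 0.70 | 98% |
| True ICC 0.8: chance that the two-sided 95% lower limit exceeds 0.70 | 52% (one-sided limit: 64%) |
| 95% interval for an observed ICC of 0.80 | 0.70 to 0.87 |
| 95% interval for an observed ICC of 0.70 | 0.57 to 0.80 |
| True ICC 0.65: chance that the estimate is at least 0.70 | 21% |
| True ICC 0.60: chance that the estimate is at least 0.70 | 6% |

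Excluding 0.70 with 80% power would need 149 returned forms (117 one-sided).

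**The case against.** **The error does no harm.** The substudy is larger than its stated inputs require. Even if only 64 of the 80 mailed forms came back (an illustrative 80% return), two-sided power against 0.6 would be 89%. The overall recruitment target of 250 rests on the Rasch calculation and is unaffected. All of this stands, and it is why the severity is limited. It does not make the sentence correct.

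**The value 0.65 is a guess.** This stands in part. It fits exactly under two-sided alpha, but the article does not state the sidedness and other departures land near 77. The authors should report what they entered rather than adopt 0.65 on a reviewer's word.

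**A benchmark for the estimate and a lower bound for precision need not be equal.** This also stands. A reader might infer that the plan contradicts itself on 0.6 and 0.70, or that the substudy has only 52% power for its own criterion. The article does not support that. It states no test against 0.70 and no rule on the confidence limit, and the wording reads naturally as a benchmark for the estimate, like the 0.70 benchmark for Cronbach's alpha in the same section. On that reading, 77 retests meet the benchmark 98% of the time if the true ICC is 0.8. The 52% holds only under a stricter rule that the article does not set.

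**The 80% completion figure does not transfer.** The 200 of 250 in the article refers to completing both visits over 12 weeks. It gives no postal return rate for the one-week form, so no shortfall in returns can be derived from it.

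**Conclusion.** The point holds in a narrow form. The stated inputs give about 50 participants (two-sided) or 39 (one-sided), not 77, and 77 gives about 94% two-sided power against 0.6. A lower limit of 0.65 with two-sided alpha is the most likely source of 77, but this is an inference.

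The substudy is not undersized for its stated limit. It is also not sized to exclude an ICC below 0.70, and the plan should say so, because an observed value just meeting the benchmark would have a confidence interval reaching down to about 0.57.

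These figures assume a one-way ICC, a true value of 0.8 where power is quoted, and all 77 forms returned. Severity is low to moderate: the stated justification is wrong, but no conclusion of the study is put at risk by the number chosen.

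**What to change.** 1. Check the calculation, keep n = 77, and restate the sentence with the inputs that produce it, including sidedness. Two consistent forms are a lower limit of 0.65, two-sided alpha 0.05, 80% power; or a lower limit of 0.6, two-sided alpha 0.05, about 94% power. Cutting the number to 50 to match 0.6 is not advised, since it would only lose precision.
2. Report the ICC with its 95% confidence interval beside the 0.70 benchmark, and say that the benchmark applies to the estimate, if that is the intention.
3. Add a sentence that 77 retests are not sized to exclude an ICC below 0.70. If the benchmark were applied to the lower 95% limit, power at a true ICC of 0.8 would be about 52% (two-sided).

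The cost is a few sentences of text. Mailing the 8-item form to more of the enrolled participants is optional. It would narrow the interval for the price of postage and data entry, but it is not needed to correct the error.

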## Discussion

CAP-RA questionnaire is a brief questionnaire that encompasses traits associated with central pain mechanisms in one tool. This is a prospective study primarily aimed at validating CAP-RA to measure and ultimately stratify central pain mechanisms in people with RA. The study is based on the premise that persistent pain in RA, in some people is caused by central mechanisms and that targeted adjuvant treatment provided to this specific population would greatly improve health outcomes in these individuals. If translated into the clinic, CAP-RA could help to assign people with RA to their optimal treatment in a more efficient manner.

The CAP-RA questionnaire will undergo rigorous psychometric testing to establish it as a validated tool to measure central pain mechanisms in individuals with RA., Pain catastrophising, depression, anxiety, neuropathic pain, pain distribution, sleep disturbance, fatigue, and depression have been found to represent a single ‘central mechanisms of pain’ trait in a population with knee osteoarthritis [28]. This current study will establish if these traits also characterise central pain mechanisms are in another musculoskeletal disorder and might therefore have general validity across a range of conditions. This study is also designed to discover if other measures of central mechanisms are able to predict future pain or fatigue, and hence to validate our underlying mechanistic hypothesis. Previously validated instruments, such as the CSI-9, PainDETECT and QST will be tested as predictors of pain or fatigue in a similar way to CAP-RA. As inflammation, specifically synovitis, is a known cause of RA pain, we will directly measure this with US to ensure that it is documented with sufficient detail and that its contribution to pain and pain prognosis is included within our analyses [67]. We predict that associations between central mechanisms and RA pain are moderated by inflammation. The scenario where synovitis resolves or improves upon commencement of a new DMARD, but pain persists, is of importance to clinicians and patients alike.

The CAP-RA questionnaire will extend the repertoire of quick and self-administered tools specifically designed to identify people with specific pain mechanisms. The CSI was designed to identify and quantify symptoms experienced by people with diagnoses such as fibromyalgia that have been associated with central sensitization. It has demonstrated good psychometric properties in multiple patient populations, but does not consider traits of neuropathic pain [36], which we have previously found to be part of the Central Mechanisms Trait in people with knee pain [68]. The originator painDETECT questionnaire has also been used to imply central pain augmentation in people with RA [38], although this alone was inferior to the central mechanisms trait in predicting PPT in people with knee pain [23]. The Allodynia Symptom Checklist is mostly used in people who suffer with headaches and has not been validated in a population with MSK pain [69, 70]. Another recently developed 11-item self-report questionnaire including items assessing pain and somatic symptoms also has not been validated in a RA population [71].

### Limitations

Although a brief questionnaire may be acceptable to patients, and feasible in busy clinical practice or large epidemiological studies, its interpretation is inevitably limited by its self-reported nature, and even validated self-report instruments are prone to recall bias. Traits assessed with the CAP-RA questionnaire are however multifaceted and subjective precluding objective measurement. We attempt to address this by testing CAP-RA against QST, as a proxy for central pain mechanisms. However, there is no gold standard for measuring CS which is itself a multidimensional construct. We will use a brief QST procedure which has been used in other research studies to measure central pain mechanisms, comprising both static (PPT) and dynamic (TS and CPM) test modalities. Each QST modality might have different measurement properties and indicate different aspects of CS including spinal processing of nociceptive signals and descending modulation. Only two timepoints will be measured, and this study was not designed to measure the ability of CAP-RA to predict persistent pain in RA beyond 3 months. This study will be conducted within a restricted geographical region (within the East Midlands of the UK) with people who have active rheumatoid arthritis measured by DAS28. Our findings might have limited generalizability outside this population. More bias may also occur with the weekly SMS text messages, as subgroup of participants opting in to this section of the study may not be representative. However, usage of SMS texting has previously been shown to be widely used in older populations with arthritis [72]. This study is reported in line with SPIRIT guidelines [32] as guidelines for cohort study protocols are not fully developed [73].

